**Figure 1 F1:**
[figure not shown]
The design and progression of participants throughout the trial will be managed, including a randomization flowchart and the protocol for intervention measurements.

### Study population

2.2

Elite-level athletes will constitute the target population, with the University Clinic of the Catholic University of Valencia as the reference center. The athletes will be recruited from the national federations of handball, basketball, and rugby. Additionally, informational pamphlets will be circulated on social media platforms, allowing for additional participant recruitment. All potential participants expressing interest will receive comprehensive details about the study procedures, including the selection process.

### Eligibility criteria

2.3

The inclusion criteria are as follows: i) individuals with a complete ACL tear diagnosed via clinical assessment and MRI scans interpreted by a board-certified radiologist; ii) patients who have undergone autologous graft ligamentoplasty; iii) individuals between 16 and 35 years of age; and iv) physically active individuals with more than 5 years of recreational sports participation. The exclusion criteria include: i) tendon, cartilage, bone, or ligament injuries requiring repair in addition to the ACL tear; ii) history of lower limb pathologies, including open surgeries, knee arthroscopies, or femur/tibia fractures; iii) presence of neuromuscular or metabolic diseases affecting the musculoskeletal system; iii) concussion within the past six months; iv) prior cranial surgery or presence of intracranial metal clips; v) use of medications affecting neuronal activity; and vi) neurological diseases or disorders.

### Procedure

2.4

After group assignment, all participants will be assessed at four scheduled time points after surgery: one month (post-surgical30), two months (post-surgical60), three months (post-surgical90), and six months (post-surgical180). Scoring scales and psychosocial assessments will be evaluated at each visit (Figure 1). All assessments will be conducted bilaterally to allow within-subject comparisons.

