**Methods/materials:**

This randomized controlled trial protocol, approved by the Ethics Committee of the Catholic University of Valencia, follows a double-blind, comparative, longitudinal design per SPIRIT guidelines. Elite athletes will be randomized 1:1 into two age- and sex-matched groups: non-invasive brain stimulation (NIBS) + rehabilitation (ProtocolRHB) or sham NIBS + ProtocolRHB. The NIBS intervention uses tDCS to deliver low-intensity direct current to modulate cortical excitability. Data collection spans April 2025 to December 2027 with outcomes assessed at four postsurgical time points. The primary outcome is electromyographic (EMG) activity to evaluate muscle activation, crucial for restoring knee stability and function. Secondary outcomes include knee function (Lysholm Scale) and ACL-specific quality of life. EEG and TMS will assess cortical excitability and plasticity during voluntary muscle contraction.

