### Study design

2.1

This study will be a randomized controlled trial featuring a double-blind, comparative, and longitudinal approach. To ensure clarity and thoroughness, the study will adhere to the SPIRIT statement guidelines (Table 1) (37). The TIDieR checklist will be used to report outcomes (38). The planned investigation will include a protocol with two comparator arms: NIBS + ProtocolRHB and ShamNIBS + ProtocolRHB, with participants randomly assigned to either arm (Figure 1). Patients will provide written informed consent prior to any study procedure, including randomization. Data collection will be conducted between April 2025 and December 2027. This study was approved by the Ethics Committee of the Catholic University of Valencia (UCV/2023-2024/053). Additionally, the study was pre-registered at https://www.Clinicaltrial.gov on 01/01/2025 (NCT06818201).

**Table 1 T1:** Execution schedule – recruitment, intervention, and reassessment.

	Study period							
	Enrolment	Allocation	Post-allocation					Close-out
Time Point	*-t_1_*	0	*t_1_*	*t_2_*	*t_3_*	*t_4_*	*T_5_*	*t_x_*
Enrolment								
Eligibility screen	X							
Informed consent	X							
Allocation		X						
Interventions								
*[NIBS* *+* *_RHB_]*								
*[SHAM_NIBS_* + _RHB_*]*								
Assessments								
*[Anthropometric data]*	X	X						
*[Psychosocial Assessment]*			X	X	X	X	X.	X
*[Scoring Scale]*			X	X	X	X	X	X
*[Functionality]*					X	X	X	X
*[EGGTMS]*			X		X		X	X
*EMGs*			X		X		X	X

t1, 2024; 0, start study; t1, postsurgical; t2, postsurgical30; t3, postsurgical60; t4, postsurgical90; t5, postsurgical180; tx, study completion.

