#### NIBS_RHB_

2.7.1

A specialized rehabilitation protocol for postsurgical ACL recovery will be implemented. This protocol, grounded in the latest clinical guidelines (43–45), will be structured into four distinct phases: i) post-surgical recovery (weeks 0–5); ii) strength and neuromuscular control (weeks 6–12); iii) running, agility, and landings (weeks 13–24); and iv) return to sport activity (after week 24). The program will encompass 72 sessions scheduled three times a week over a 24-week period. Strength training will be the primary focus of all phases. To ensure optimal patient progress, regular assessments will be conducted with advancement to subsequent recovery phases based on the specific criteria. A schematic representation of the exercise protocol will be employed during rehabilitation (Table 2).

**Table 2 T2:** Phased rehabilitation protocol following ACL reconstruction: objectives, progression criteria, and recommended exercises.

Phase		Weeks	Objectives	Progression criteria	Recommended exercises
Post-surgery recovery	PHASE 1.1	0–2	• Achieve fully extend the knee • Reduce inflammation • Activate the quadriceps • Full extension (0°) • Active quadriceps contraction	• Full extension (0°) • Active quadriceps contraction • Quadriceps Lag Test	• Straight leg raise (SLR): flexion, extension, abduction and adduction • Peripheral joint mobilization • Isometric quadriceps at 90°–60° • Gait training • Inflammation management: cryotherapy + compression
	PHASE 1.2	3–5		• Extension 0° • Contralateral flexion −10° • Absence of inflammation (stroke test)	Strength: • Squat (0°–60°) • Hamstring Curl • Step Up → Step Up + running technique • Lumbo-pelvic strengthening: Clamshell, Side-Lying Leg Raise Bilateral/Unilateral, Hip Hike Balance: • Progression from bilateral to single leg stance • Stationary cycling >100°
Strength and motor control	PHASE 2.1	6–8	• Restore knee strength • Restore muscle strength • Execute Single Leg Stance with proper technique	• Absence of edema • Absence of pain/edema post-exercise • Full Range of Motion (ROM) • Normal gait pattern	• Leg press, Hamstring curl, Hip abduction and adduction, Knee extension (90°–45°), Air squat with band, Deadlift • Single leg squat (SLS) progression • Progression of unilateral balance exercises to include perturbations

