Furthermore, the tDCS device from Ionclinics will be used in the study. The device will be applied during the early stage of rehabilitation, specifically during activation, as the exercises required will be less demanding, less intricate, and more appropriate for this intervention. The treatment plan includes 16 sessions over an 8-week period, with two sessions each week. Each session will administer a continuous current of 2 mA for 20 min. The setup comprises two electrodes (a red anode and a black cathode) and two sponge pads with conductive gel, all incorporated into a helmet tailored to the patient. Electrode placement will adhere to the international 10–20 system for tDCS (46). The primary motor cortex (M1) will be the focus of stimulation, with the anode placed at either C3 or C4, corresponding to the hemisphere contralateral to the injured leg, to target the affected motor area. The cathode will be positioned at the opposite supraorbital area, either Fp1 or Fp2. This placement ensures that stimulation is applied to the motor cortex controlling the injured limb, which is critical for modulating cortical excitability and enhancing the neuromuscular control. The tDCS stimulation will be applied prior to this early rehabilitation phase to ensure proper monitoring and to maximize the safety and efficacy of the intervention*.* The tDCS stimulation will be applied prior to this early rehabilitation phase. Specifically, during the Post-Surgery Recovery Phases 1.1 and 1.2, as well as the Strength and Motor Control Phase 2.1.

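### Table 1 places the primary EMG outcome at a post-surgical visit (t1) and an undated close-out (tx) that section 2.4 does not list; if section 2.4 is followed, no EMG precedes stimulation

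*Protocol article*

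**What the plan says.** **Visits in section 2.4 (Procedure).** After group assignment, "all participants will be assessed at four scheduled time points after surgery: one month (post-surgical30), two months (post-surgical60), three months (post-surgical90"); the fourth time point is six months (day 180). The section adds that "Scoring scales and psychosocial assessments will be evaluated at each visit". It does not name EMG and lists no visit before day 30.

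**Visits in section 2.1, Table 1.** The key reads "t1, postsurgical; t2, postsurgical30; t3, postsurgical60; t4, postsurgical90; t5, postsurgical180; tx, study completion". The EMG row is marked at t1, t3 (day 60), t5 (day 180) and tx. It is empty at t2 (day 30), at t4 (day 90) and in the two columns before t1.

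**Abstract.** It gives a count without dates: "with outcomes assessed at four postsurgical time points".

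**Stimulation course, section 2.7.1.** "The treatment plan includes 16 sessions over an 8-week period, with two sessions each week", given "during the Post-Surgery Recovery Phases 1.1 and 1.2, as well as the Strength and Motor Control Phase 2.1". The rehabilitation clock is "post-surgical recovery (weeks 0–5); ii) strength and neuromuscular control (weeks 6–12"), and Table 2 puts phases 1.1, 1.2 and 2.1 at weeks 0–2, 3–5 and 6–8.

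**Analysis, section 2.10.2.2.** A repeated measures ANOVA assesses time, group and interaction effects for primary and secondary outcomes.

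**The concern.** The times at which the primary outcome is measured should be the same wherever the protocol gives them. Here one section leaves out a visit at which the schedule table places the primary measurement, and that visit is the only candidate for an EMG taken before stimulation.

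Two things are at stake. First, the EMG series is not fixed: depending on which section is followed, it may or may not start before day 30, and it may or may not include a last measurement at an unstated date. Second, a group-by-time interaction measures how the groups diverge over the measured visits. If the first of these falls in mid-course, any treatment effect already gained and then held is constant across visits, and the interaction cannot see it. An EMG that was not taken before stimulation cannot be recovered later.

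**Working it through.** **Step 1. The two schedules side by side.**

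| Visit | Section 2.4 | Table 1, EMG row |
|---|---|---|
| t1, postsurgical | not listed | marked |
| day 30 | listed | empty |
| day 60 | listed | marked |
| day 90 | listed | empty |
| day 180 | listed | marked |
| tx, study completion | not listed | marked, no date |

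Because section 2.4 does not name EMG, the empty cells at days 30 and 90 can mean that EMG is done at only some visits. That is no conflict. The t1 and tx rows are, because section 2.4 has no such visits. The abstract's count of four fits both the four days of section 2.4 and the four EMG marks of Table 1, so it does not settle the matter.

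**Step 2. Is another pre-stimulation EMG described?** The baseline list in section 2.8.1 does not include EMG. The baseline EMG in section 2.8.2.2 is a resting segment of a recording, not a visit before treatment. That leaves t1. It stands among the post-allocation columns, and the readable text does not say that it precedes the first session.

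**Step 3. Sessions given by day 30** (two per week, 16 in all).
- Start at week 0: 2 × 30/7 = 8.6 sessions; 8.6/16 = 54%.
- Start at the end of week 2 (assumption, the latest start still within phase 1.1): 2 × (30 − 14)/7 = 4.6 sessions; 4.6/16 = 29%.

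So roughly 5 to 9 of the 16 sessions precede the first visit of section 2.4. If EMG were taken only at the dated visits common to both places (days 60 and 180), a week-0 start would put all 16 sessions before the first EMG (2 × 60/7 = 17.1, capped at 16).

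**Step 4. The plan's own figure.** Section 2.6 states 46 participants before dropout, for an effect of 0.357, power 0.95 and alpha 0.05. This can be neither confirmed nor refuted, because the number of measurements, their correlation and the effect tested are not given. Taking 0.357 as Cohen's f and a correlation of 0.5, the interaction test needs 20 participants with four measurements and 22 with three; the between-group test needs 66 and 70. The 95% below is therefore attached to a generic contrast, as an assumption.

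**Step 5. Loss in a contrast against the first visit.** For 95% power at two-sided 5%, the noncentrality is 1.960 + 1.645 = 3.605. If a share p of the effect is present at the first visit and held, the contrast keeps (1 − p) of it, and power = P(Z > 1.960 − 3.605(1 − p)).
- p = 0: 95%, unchanged.
- p = 0.29: 3.605 × 0.71 = 2.56; P(Z > −0.60) ≈ 73%.
- p = 0.50: 3.605 × 0.50 = 1.80; P(Z > 0.16) ≈ 44%.

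**Step 6. The same question in the planned model.** Assumptions: d = 2 × 0.357 = 0.714, 23 per arm, equal correlation of 0.5 between visits, full effect from day 60 on. Let d_j be the group difference at visit j, and m the number of visits.
- Interaction noncentrality: (23/2) × Σ(d_j − mean)² / (1 − 0.5).
- Group main effect noncentrality: (23/2) × m × mean² / (1 + (m − 1) × 0.5).

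| EMG visits | Interaction power | Group main effect power |
|---|---|---|
| t1 as true pre-stimulation baseline, 60, 180 | 0.69 | 0.49 |
| 30, 60, 90, 180 with 54% of the effect at day 30 | 0.18 | 0.76 |

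For 27% to 75% of the effect present at day 30, interaction power runs from 0.40 to 0.08. With none present it is 0.69.

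**Step 7. Value of a true baseline as covariate.** For a single-visit comparison with d = 0.714 and 23 per arm, the noncentrality is 0.714 × √(23/2) = 2.42, which gives power of about 66%. Adjusting for a baseline with correlation r replaces d by d/√(1 − r²).
- r = 0.2: 0.729, about 68%.
- r = 0.5: 0.824, about 78%.
- r = 0.7: 1.000, about 91%.

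**The case against.** Several points on the other side stand.

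- **The two schedules do not conflict throughout.** A reader might infer that section 2.4 requires EMG at days 30 and 90 and that Table 1 omits it. Section 2.4 does not name EMG, so the documents do not support that. Nor does the abstract contradict Table 1, since it gives no days. The conflict is confined to t1 and tx.
- **The timing of t1 may be shown elsewhere.** The intervention rows of Table 1 are blank in the readable text, and Figure 1, to which section 2.4 refers, is not visible. Bars or arrows there may place t1 before the first session. A baseline taken after allocation but before treatment would be sound.
- **The trial does not lose its treatment comparison.** The planned group main effect keeps an effect present by day 30, remains valid under randomisation, and in the illustration has more power with the visits of section 2.4 (0.76) than with those of Table 1 (0.49).
- **How t1 enters the model is not stated.** A reader might infer that it is one more level of the time factor. Section 2.10.2.2 does not say so, and an analysis plan that is not shown may settle it.

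What this does not remove is that a listed primary-outcome visit is absent from the procedure section, and that the readable text nowhere says that any EMG precedes stimulation.

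**Conclusion.** The point holds in a limited form. Section 2.4 and Table 1 disagree on t1 and tx for the primary outcome, and following section 2.4 would leave the trial without a pre-stimulation EMG. The harm falls on the group-by-time interaction only.

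Its size is not fixed by the documents. It rests on how much of the effect is present by day 30, when stimulation starts, the correlation between visits, and the reading of 0.357 as Cohen's f. A contrast with 95% power would fall to about 44% or 73%, or not at all, in the three cases shown. A reader might take the 44% as the power of the trial; it is one assumed scenario for one of the planned tests.

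The contradiction needs none of these assumptions. It should be resolved before EMG data are collected, because a missed early measurement cannot be made up.

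**What to change.** 1. Make Table 1 the operative EMG schedule and add t1 to the visit list in section 2.4. Word the abstract's count to match.
2. State that the t1 EMG is taken before the first tDCS session.
3. Give tx a date relative to day 180, or drop it for EMG.
4. Use t1 EMG as a baseline covariate, with days 60 and 180 as the outcomes.
5. Reconcile with Table 2 which EMG tasks are performed on the operated leg at t1. The covariate should be a task actually performed then.

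Cost: mostly protocol wording, since the t1 EMG is already in Table 1. The practical burden is that t1 must be booked before the first stimulation. The covariate brings little if t1 EMG correlates weakly with later EMG, with about two percentage points of power gained at a correlation of 0.2.

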### Randomization and blinding

2.5

A block randomization design with block sizes of 4 or 6 will be implemented to ensure an even distribution of participants across groups. A double-blind design will be employed, ensuring that both the patients and the evaluators collecting data on the study variables are blinded to the adjunctive effect of complementary tDCS during the rehabilitation. To assess blinding, one might apply the recommendations of Bang et al. (39, 40). We will implement a close-ended questionnaire to enquire participants and technicians about treatment assignment with the following questions:

Question 1: “What tDCS treatment do you believe you have received/applied?” The participants/technicians will be asked to choose from three possible answers: (1) real current, (2) simulated current, or (3) do not know. If participants or therapists answered Do not know’, then Question 2 was asked: “Please provide your best guess about the tDCS treatment you received/applied and asked to choose from two possible replies”: (1) real current; (2) simulated current. Finally, we will ask for a confidence assessment with Question 3: “For the tDCS treatment you chose in question 1 or 2, please provide on a scale of 0–10 the level of confidence you have in being correct, where 0 means you are totally guessing and 10 means you are completely sure”.

### Sample size

2.6

The required sample size was determined using GPower® software (Franz Faul, Universität Kiel, Kiel, Germany), version 3.1.9.2. A preliminary sample of 46 subjects, divided into two groups of 23 participants each, was established for the intervention design. The primary variable (EMG output) was used for statistical analysis through repeated measures ANOVA. Cohen's effect size was set at 0.357 based on a previous study examining using surface EMG recordings as their primary outcome (41). The calculation incorporated a statistical power of 0.95, an alpha level of 0.05, and two intervention groups. To account for potential dropouts during treatment follow-up (estimated at 15%), an additional 3 participants were added to each group. This resulted in a total of 54 participants, with 27 per group. The chosen effect size, exceeding 0.357, is classified as “moderate” (42). If a greater percent of participants does not follow their planned treatment protocol (dropouts, non-adherence to treatment, or missing results), an “intention-to-treat” analysis will be conducted.

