##### Analysis of the outcome measures

2.10.2.2

A per-protocol analysis will be performed in accordance with the CONSORT guidelines for reporting randomized controlled trials. The Kolmogorov–Smirnov test will be utilized to verify the normality assumption, and the Levene test will be used to evaluate the homogeneity of variances. To examine the effects of tDCS combined with exercise-based rehabilitation on patients undergoing ACL reconstruction, repeated measures ANOVA will be applied, with experimental groups as factors and Bonferroni corrections for *post hoc* analysis. Comparisons within and between groups for both primary and secondary outcomes will assess time, group, and interaction effects. Results will be expressed as mean differences (MD) with 95% confidence intervals (CI95%). The effect size (ES) will be calculated using Cohen's d coefficient. All statistical analyses will be conducted using SPSS 24 software (IBM Inc., Chicago, Illinois, USA). If there are participant dropouts or if the statistical power is below 80%, an intention-to-treat analysis will be implemented (78).

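### Section 2.6 adds 3 to 23 per group and reports 27: the addition gives 26 (52 in total), and 3 is too few for the stated 15% dropout, whereas 27 (54) is adequate

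*Protocol article*

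**What the plan says.** Section 2.6 (Sample size) reports a G*Power calculation. Its starting figure is "A preliminary sample of 46 subjects, divided into two groups of 23 participants each". On the method it says "The primary variable (EMG output) was used for statistical analysis through repeated measures ANOVA", and on the effect "Cohen's effect size was set at 0.357 based on a previous study". The remaining inputs are given as follows: "The calculation incorporated a statistical power of 0.95, an alpha level of 0.05, and two intervention groups". Dropout is put at 15%, and the section continues "an additional 3 participants were added to each group. This resulted in a total of 54 participants, with 27 per group". A later sentence describes the chosen effect as larger than 0.357, although the section has just fixed it at exactly that value.

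The section does not say which ANOVA effect was powered (group, time or interaction), how many measurements entered the calculation, what correlation between repeated measurements was assumed, or whether 0.357 is Cohen's f or d. Section 2.10.2.2 plans to examine time, group and interaction effects, and names Cohen's d as the effect size for reporting results.

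**The concern.** The recruitment target is a figure that the ethics committee, the funder and readers all rely on, and here it can be read as 52 or as 54. The two readings are not equivalent: one meets the section's own dropout assumption and the other does not. No fuller document could reconcile the two statements, because both are explicit and they disagree.

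The starting figure of 46 raises a lesser question. If it cannot be traced to stated inputs, a reader cannot tell what the 95% power refers to: a difference between arms averaged over visits, or a difference in the course over time. For the same numerical effect size these two need very different sample sizes.

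**Working it through.** **Addition.** Inputs from section 2.6: 23 per group, 3 added per group, final 27 per group and 54 in total.

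- 23 + 3 = 26 per group; 2 x 26 = 52 in total.
- Reaching 27 per group needs 27 - 23 = 4 added; 2 x 27 = 54. The stated 27 and 54 agree with each other, so the 3 is the odd figure out.

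**Dropout.** Input from section 2.6: 15%.

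- Enrolment needed: 23/0.85 = 27.06 per group; 46/0.85 = 54.1 in total.
- With 27 per group: 27 x 0.85 = 22.95; 54 x 0.85 = 45.9. Losing 4 of 27 (14.8%) leaves exactly 23.
- With 26 per group: 26 x 0.85 = 22.1; 52 x 0.85 = 44.2. Losing 3 of 26, which leaves 23, is only 11.5%.

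The total of 54 therefore matches the stated dropout within rounding, and the stated addition of 3 does not.

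**The 46 for 95% power.** Inputs from section 2.6: effect size 0.357, alpha 0.05, power 0.95, two groups, repeated measures ANOVA. Assumptions, because the section gives no values: 0.357 is f, sphericity holds, m = 2 to 6 measurements, within-person correlation rho = 0.5. Noncentral F with

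- between-group effect: lambda = f² N m / (1 + (m - 1) rho), df 1 and N - 2;
- group-by-time interaction: lambda = f² N m / (1 - rho), df m - 1 and (N - 2)(m - 1).

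Example, between-group effect with m = 4 and N = 46: lambda = 0.357² x 46 x 4 / 2.5 = 9.38, power 0.85.

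| m | N for 95%, interaction | N for 95%, between-group | Power at N = 46, between-group |
|---|---|---|---|
| 2 | 28 | 80 | 0.78 |
| 3 | 22 | 70 | 0.83 |
| 4 | 20 | 66 | 0.85 |
| 5 | 16 | 64 | 0.86 |
| 6 | 16 | 62 | 0.87 |

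At rho = 0.5 neither column of required N contains 46; it falls in the gap between them. Interaction power at N = 46 is above 0.99 for every m in the table.

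Other values of the unstated settings do return 46:

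- between-group effect, m = 4, rho = 0.23: N = 46 (power 0.954);
- between-group effect, m = 6, rho = 0.3: N = 46 (power 0.956);
- interaction, m = 2, rho = 0.15: N = 46 (power 0.953);
- 0.357 read as d, so f = 0.357/2 = 0.1785, interaction, m = 4, rho = 0.67: N = 46 (power 0.951).

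These settings differ in the effect tested, the number of measurements, the correlation and the metric. The stated inputs thus do not determine N.

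**The case against.** On the addition, the best defence is that this is a slip in one word: 27 and 54 are consistent with each other and with 15% dropout, so the design is unharmed. That is fair, and it is why the remedy is small. It does not remove the contradiction.

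On the 46, the defence is stronger. Correlation, number of measurements and sphericity correction are details that an article often leaves to a full protocol or analysis plan, and plausible values reproduce 46. Since G*Power's repeated measures ANOVA takes f, and Cohen's d appears only for reporting results, f is the more natural reading. The interaction is among the planned effects, and at rho = 0.5 it would be more than adequately powered. All of this stands, and it limits the point to one of verification.

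A reader might draw three stronger conclusions that the documents do not support:

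- *27 per group fails to cover 15% dropout, so 28 per group (56) are needed.* Rounding 27.06 up strictly does give 28, but the shortfall at 27 is 0.05 of a participant per group.
- *46 is wrong and 0.95 should be replaced by about 83%.* That figure assumes the between-group effect, three measurements and a correlation of 0.5, none of which the section states.
- *Calling the effect moderate is wrong.* On the usual benchmarks for f (0.25 medium, 0.40 large), 0.357 is above medium and below large, so the label can stand.

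**Conclusion.** The contradiction is certain and needs no assumption: 23 + 3 is 26 per group (52), not 27 (54). The difference is one participant per group, two in total. It matters because an allowance of 3 leaves 22.1 expected completers per group against 23 required, whereas 27 leaves 22.95. The error lies in the number added, and the target of 54 can stand.

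The 95% power claim is unverifiable, not refuted. At f = 0.357 and rho = 0.5, the required N is 16 to 28 for the interaction and 62 to 80 for the between-group effect; at other unstated settings it is 46. That range rests on the noncentral F formulas above with sphericity and f as the metric. The wording on the effect size, first set at 0.357 and then described as exceeding it, is a small inconsistency in the same section.

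**What to change.** 1. In section 2.6, change the number added from 3 to 4 per group and keep 27 per group, 54 in total.
2. State the inputs behind 46: the ANOVA effect that was powered, the number of EMG measurements, the within-person correlation, and whether 0.357 is f or d.
3. Keep 0.95 if those inputs reproduce 46. If they do not, state the power delivered for the intended effect; for example, about 83% to 86% if that was the between-group effect over 3 to 5 measurements at f = 0.357 and correlation 0.5.
4. Reconcile the two descriptions of the effect size, so that it is either 0.357 or a stated larger value.

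The cost is rewording one section. No additional patients are needed and the analysis does not change. The only possible loss is a less favourable power figure, should item 3 require one.
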